# The effect of perioperative of dexamethasone on postoperative complications after pancreaticoduodenectomy (PANDEX): a study protocol for a pragmatic multicenter randomized controlled trial

**DOI:** 10.1186/s13063-023-07571-y

**Published:** 2023-09-02

**Keywords:** Pancreaticoduodenectomy, Dexamethasone, Postoperative complications

## Abstract

**Background:**

Pancreaticoduodenectomy (PD) nowadays serves as a standard treatment for patients with disorders of the pancreas, intestine, and bile duct. Although the mortality rate of patients undergoing PD has decreased significantly, postoperative complication rates remain high. Dexamethasone, a synthetic glucocorticoid with potent anti-inflammatory and metabolic effects, has been proven to have a favorable effect on certain complications. However, the role it plays in post-pancreatectomy patients has not been systematically evaluated. The aim of this study is to assess the effect of dexamethasone on postoperative complications after PD.

**Methods:**

The PANDEX trial is an investigator-initiated, multicentric, prospective, randomized, double-blinded, placebo-control, pragmatic study. The trial is designed to enroll 300 patients who are going to receive elective PD. Patients will be randomized to receive 0.2 mg/kg dexamethasone or saline placebo, administered as an intravenous bolus within 5 min after induction of anesthesia. The primary outcome is the Comprehensive Complication Index (CCI) score within 30 days after the operation. The secondary outcomes include postoperative major complications (Clavien-Dindo≥3), postoperative pancreatic fistula (POPF), post-pancreatectomy acute pancreatitis (PPAP), infection, and unexpected relaparotomy, as well as postoperative length of stay, 30-day mortality, and 90-day mortality.

**Discussion:**

The PANDEX trial is the first randomized controlled trial concerning the effect of dexamethasone on postoperative complications of patients undergoing PD, with the hypothesis that the intraoperative use of dexamethasone can reduce the incidence of postoperative complications and improve short-term outcomes after PD. The results of the present study will guide the perioperative use of dexamethasone and help improve the clinical management of post-pancreatectomy patients.

**Trial registration:**

ClinicalTrials.gov NCT05567094. Registered on 30 September 30 2022

**Supplementary Information:**

The online version contains supplementary material available at 10.1186/s13063-023-07571-y.

## Background

Pancreaticoduodenectomy (PD)—also known as a Whipple procedure—is a complex operation that is used to treat tumors and other disorders of the pancreas, intestine, and bile duct. After the demanding resection, pancreatic-enteric, biliary-enteric, and gastrojejunal anastomoses are required to complete digestive tract reconstruction. Pancreatic-enteric anastomosis has remained a true Achilles’ heel in this complex and technically demanding operation. Despite improvements in operative techniques and perioperative management, the incidence of postoperative complications after PD remains high [1–3]. The main postoperative complications include postoperative pancreatic fistula (POPF), post-pancreatectomy hemorrhage (PPH), and delayed gastric emptying (DGE).

In recent years, post-pancreatectomy acute pancreatitis (PPAP) has been recognized as an independent complication after pancreatic resections [4–7]. Major surgery induces both local and systemic inflammation. A series of events related to operative trauma, ranging from manipulation, mobilization, alteration of blood supply, and/or stasis of pancreatic juice, appear to play a fundamental role in the etiology of PPAP [4, 8, 9]. These pathophysiological events may trigger a series of cascading events causing acinar cell disruption, intracellular activation of proteolytic enzymes, pancreatic parenchymal edema, and peripancreatic inflammation, leading to local and/or systemic effects [10]. Therefore, it is assumed that this inflammatory cascade of the remnant pancreas in the early postoperative reaction could be the possible mediator that triggers further downstream PD-related complications, particularly POPF and DGE [8, 11–14].

Dexamethasone is a synthetic glucocorticoid with potent anti-inflammatory and metabolic effects. In addition, a low dose of dexamethasone is frequently administered in the perioperative period, most commonly for prophylaxis of postoperative nausea and vomiting [15]. The mechanism of dexamethasone is poorly understood, but it seems to be most effective when it is administered before the start of surgery, as it can also reduce surgery-induced inflammation [16]. It is assumed that the antiemetic effect of dexamethasone is possibly related to its anti-inflammatory actions in the gastrointestinal tract.

Prolonged use of steroids such as dexamethasone can have dangerous side effects, including an increased risk of wound infection and anastomotic leak, which adversely affect recovery from gastrointestinal surgery. Although a single dose does not seem to be associated with these increased risks, it is reported that a single dose of dexamethasone was associated with hyperglycemia in surgical patients [17–19]. Though the DREAMS trial demonstrated that a single dose of 8 mg dexamethasone at induction of anesthesia could reduce nausea and vomiting rate after gastrointestinal surgery [20], concerns about the side effect among the surgical community might still be limiting its use during abdominal surgery. The PADDI trial confirmed that 8 mg dexamethasone was non-inferior to placebo with respect to the risk of surgical-site infection [19]. But few pancreatic surgeries are included in this study. Because PD consists of three anastomoses, the failure of which could result in dreaded complications, perioperative administration of dexamethasone has not been widely implemented into clinical practice in the setting of PD surgery. Recently, the Finland RCT reported that perioperative hydrocortisone significantly reduced postoperative complications after PD in high-risk patients [14]. In addition, PPAP is a series of early postoperative inflammatory reactions caused by the remnant pancreas. If the inflammation could be diminished, then the incidence of postoperative complications can be effectively reduced. Therefore, this study aims to assess the effect of dexamethasone on postoperative complications after PD.

## Methods/design

### Study design

The PANDEX trial is an investigator-initiated, multicentric, prospective, randomized, double-blinded, placebo-control, pragmatic study. The trial will be conducted in seven high-volume centers in China (>50 PDs per year). This study hypothesizes that the intraoperative use of dexamethasone can reduce the incidence of postoperative complications after PD. The flowchart of this study is shown in Fig. 1. This article adheres to the Standard Protocol Items: Recommendations for Interventional Trials (SPIRIT) statement [21, 22].

**Fig. 1 Fig1:**
[figure not shown]
Study flowchart. Dex, dexamethasone; POD, postoperative day; CBC, complete blood count; CRP, C-reactive protein; CT, computed tomography

### Participants

Patients who are going to receive elective PD in the participating centers will be reviewed for eligibility. A screening form will be used to exclude those who do not meet the following criteria. The inclusion criteria were as follows: (1) adult patients ≥18 years of age, (2) an indication for elective PD surgery, (3) patients understand the nature of this trial and are willing to comply, and (4) patients are able to provide written informed consent. The exclusion criteria were as follows: (1) current or recent (within preceding 1 month) systemic use of glucocorticoids; (2) distant metastases including peritoneal carcinomatosis, liver metastases, distant lymph node metastases, and involvement of other organs; (3) palliative surgery; (4) patients with high operative risk, as defined by the American Society of Anesthesiologists (ASA), with a score ≥ 4; (5) synchronous malignancy in other organs or second cancer requiring resection during the same procedure; (6) pregnancy; and (7) enrolled in other trials.

### Participant enrollment and withdrawal

Eligible patients will be assessed and informed by the specific study coordinators at the in-patient department. Recruited patients will be informed further in detail and will sign a written informed consent prior to treatment initiation, which can be revoked at any time. The duration of the recruitment period is estimated to be an 18-month interval depending on the recruiting rate. No financial incentives will be provided to the trial investigators or patients for enrolment during the recruitment period. All the patients will be free to participate in this study and can decide to withdraw at any time. If a patient withdraws, his/her information will not be recorded in the study.

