### Data management and monitor

In this study, the Guancui EDC system will be used for data collection. Patient data will be documented by dedicated trial personnel and managed in the eCRF. Data will be entered through a dedicated WeChat applet or web browser input masks. All staff involved in the data collection process are to be qualified to access the research database. Data collection must be collected in accordance with standard specification processes. The system cannot automatically identify the data needed to enter through manual input by the data entry person. All study-related information and participant information will be stored securely at the study site with locked cabinets in areas with limited access. The database will be secured with a password-protected access system.

An independent Data and Safety Monitoring Committee (DSMC) will be appointed to evaluate the study safety parameters. The DSMC will exist of two independent statisticians and two independent surgeons. DSMC members will meet before trial initiation, 3 months after the inclusion of the first patient, thereafter every 6 months, and after the interim analysis. All adverse events will be recorded on the eCRF. If the DSMC identify safety issues, they will have the prerogative to request unblinded outcomes. The safety of this trial will be evaluated in standardized intervals by the appointed institutional ethics and DSMC, which will advise regarding the trial’s status. More specifically, 30-day mortality will be monitored independently in each arm, and if a safety threshold of 5% is reached at any given time, the trial will be withheld for further safety evaluation and potential decision for early termination.

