#### General analysis principle

Normality will be examined using the Shapiro-Wilk test. For normal distribution, continuous variables will be described as mean and standard deviation (SD) and compared using the *t*-test. For non-normal distribution, continuous variables will be described as medians and interquartile range (IQR) and compared using the Mann-Whitney test. test. Categorical variables will be expressed as frequencies and percentages and compared using chi-squared test or Fisher exact test when appropriate. We have no imputation plans for missing data. All statistical tests will be tested with two sides, *P* < 0.05 is considered to represent a statistically significant difference, with a CI of 95%. All analyses were performed using Stata (Stata Corporation, version 15, College Station, TX, USA).

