#### Efficacy analysis

All outcomes will be analyzed using modified intention-to-treat analyses, where all randomized patients who undergo scheduled pancreaticoduodenectomy were included in the analyses. Criteria to remove patients from analyses after randomization are as follows:Scheduled pancreaticoduodenectomy was not performed (e.g., disseminated cancer, enucleation).Total pancreatectomy was performed.Additional hepatic resection.Patient withdrew consent prior to surgery.

The primary outcome is a sum of all complications that are weighted for their severity, based on the Clavien-Dindo classification, the Comprehensive Complication Index (CCI). CCI score will be presented as mean ± SD and in case of skewed distributions as median and range. Values will be compared by the *t*-test or the Mann-Whitney test as appropriate.

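### The protocol does not record the information of any patient who withdraws, with no time limit, which conflicts with its modified ITT set and its adverse-event rule

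*Protocol article*

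**What the plan says.** Four statements in the protocol article bear on a patient who withdraws.

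- *Participant enrollment and withdrawal*: patients "can decide to withdraw at any time", and "If a patient withdraws, his/her information will not be recorded in the study". Neither statement is limited to a period of the trial or to data not yet collected.
- *Efficacy analysis*: "All outcomes will be analyzed using modified intention-to-treat analyses, where all randomized patients who undergo scheduled pancreaticoduodenectomy were included in the analyses". Four grounds for removal after randomisation follow. Three are surgical; the only one about withdrawal is "Patient withdrew consent prior to surgery".
- *Data management and monitor*: "All adverse events will be recorded on the eCRF". The same section adds that "30-day mortality will be monitored independently in each arm, and if a safety threshold of 5% is reached at any given time", the trial is held for safety evaluation.
- *General analysis principle*: "We have no imputation plans for missing data".

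**The concern.** The study drug is a single bolus given just after induction of anaesthesia, so everyone who withdraws after surgery has been fully exposed and may already have had complications. The CCI accrues over 30 days and mortality is counted to 90 days, which leaves a long period in which withdrawal can follow a bad course. If such patients leave no record, their complications and deaths are missing from the primary endpoint, from the secondary endpoints and from what the monitoring committee sees. The Background itself raises wound infection and anastomotic leak as worries with steroids, so under-counted harms matter here. The comparison between arms is also at risk if the reasons for withdrawal are linked to outcome and to treatment.

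**Working it through.** **1. The rules side by side**

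| Time of withdrawal | Withdrawal section | Efficacy analysis | Adverse-event rule |
|---|---|---|---|
| Before surgery | Not recorded | Removed | Nothing after dosing to record |
| After dosing and surgery | Not recorded | Kept in the modified ITT set | All events recorded |

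The first row is consistent. The second is not: the patient belongs to the analysis set but has no data, and the events must be recorded and not recorded. Without imputation the patient drops out of the comparison.

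**2. Two readings of the withdrawal sentence**

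- Literal: nothing about the patient is kept. The 30-day CCI, 30-day and 90-day mortality and the patient's place in the 5% monitoring are all lost.
- Prospective: recording stops at withdrawal. Earlier entries remain, but later complications and deaths are lost. Table 2 marks the primary and secondary outcomes at day 30 only, so it is unclear whether a CCI would exist for someone who left sooner.

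The conflict with the analysis set is sharpest under the first reading, but later events are lost under both.

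**3. What the plan says about numbers lost**

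The only related figure is the 20% allowance that takes 128 per group to 150. Multiplying gives 128 × 1.20 = 153.6, close to 150; dividing gives 128 / 0.80 = 160. The allowance covers dropout and protocol deviations together, so it yields no withdrawal rate.

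**4. Effect on the mean CCI (illustration)**

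Inputs: n = 150 per arm (*Sample size calculation*); single-complication CCI values from Table 1; arm mean m assumed, because the protocol gives none. Losing one patient with score c lowers the arm mean by m − (n·m − c)/(n − 1) = (c − m)/(n − 1).

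| Grade (c) | m = 18 | m = 25 |
|---|---|---|
| IIIa (26.2) | 8.2/149 = 0.055 | 1.2/149 = 0.008 |
| IIIb (33.7) | 15.7/149 = 0.105 | 8.7/149 = 0.058 |
| IVa (42.4) | 24.4/149 = 0.164 | 17.4/149 = 0.117 |

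For k such patients the shift is k(c − m)/(n − k). Five at grade IVa with m = 25 give 5 × 17.4/145 = 0.60.

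**5. Effect on the mortality threshold (illustration)**

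- Full arms: 8/150 = 5.3% reaches 5%; with one of these patients unrecorded, 7/149 = 4.7% does not.
- 75 per arm: 4/75 = 5.3% becomes 3/74 = 4.1%.

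Both cases need a patient who withdraws and then dies within 30 days.

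**6. Stress test of the type I error**

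A simulation (4,000 repetitions, 150 per arm, no true effect, an assumed CCI distribution) took all withdrawals from one arm and from patients with CCI of at least 26.2. Rejection rates for Mann-Whitney / t-test were 5.2% / 4.9% with no withdrawals, 6.7% / 6.0% with 5 and 20.3% / 16.4% with 15. The set-up is deliberately one-sided and its pool of withdrawals includes some patients with CCI 100, so it marks an unfavourable edge, not an expectation.

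**The case against.** The strongest defence is that the sentence does not say collected data are deleted. It may mean only that recording stops, and the full protocol (version 2.1) and the consent terms are not shown. That stands as far as it goes: a reader might infer that withdrawn patients are wiped from the database, but this is only the literal reading. It does not remove the point, because the article states a rule without a time limit, and the milder reading still loses later events.

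The second defence is that bias is not shown. It needs withdrawals that are related to outcome and unequal between arms. Patients, surgeons, data collectors and assessors are blinded, and there are no extra visits to prompt late withdrawal. This also stands. Blinding is not complete, since study coordinators know the allocation and coordinators also assess and inform patients; the article does not say who handles withdrawals. Under-counting of harms needs no difference between arms.

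Three stronger inferences are not supported:

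- *That the full 20% (60 of 300) could be lost this way.* The allowance includes protocol deviations, and no withdrawal rate is stated.
- *That a lost patient typically scores CCI 100.* That score belongs to death, so the patient would have to withdraw first and die afterwards. Living patients with one complication of grade IIIa to IVa give the much smaller shifts shown above.
- *That the surgical removals from the modified ITT set are part of the same error.* They are a declared choice, made at operation by blinded surgeons, and the 5% mortality rule is not tied to that set.

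**Conclusion.** The conflict is in the text and should be resolved. The withdrawal sentence cannot be followed together with the modified ITT definition and the adverse-event rule for anyone who withdraws after surgery. The consequence is a risk of under-counted harms, and of a biased CCI comparison under the two conditions named above; neither is demonstrated. The size is unknown for want of a withdrawal rate. Per lost patient with a single grade IIIa to IVa complication, the shift in an arm mean is small: at most 0.164 points at an assumed mean of 18, and less at 25. It becomes material only if several such losses fall in one arm. The mortality monitoring is more sensitive, because close to 5% one unrecorded death can decide whether the threshold is reached.

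**What to change.** - In *Participant enrollment and withdrawal*, limit the non-recording sentence to patients who withdraw before surgery.
- For later withdrawals, state that data collected up to withdrawal are retained and analysed in the modified ITT set, as far as the signed consent allows. A CCI truncated at withdrawal is a lower bound for the 30-day score and should be reported as such.
- Ask these patients whether 30-day complications and 30-day and 90-day vital status may still be collected.
- Record the date and reason of each withdrawal and report them by arm.
- Align this section with *Data management and monitor* and *Efficacy analysis*, so that one rule governs the eCRF, the monitoring and the analysis set.

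The sample size does not change. The cost is protocol and consent wording. With 120 patients recruited at submission, those already enrolled may be bound by the terms they signed, and some patients will refuse further follow-up. The change is best made early, since data never recorded may not be recoverable at analysis. A table of mortality and infection in all dosed patients would be a useful optional addition, but this correction does not depend on it.

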### Randomization

After enrollment, randomization and allocation will be done on the day of surgery. The randomization will be centralized in the Guancui EDC system. We applied a randomized block design with a block number of six in a 1:1 ratio. A data manager who is independent of the data analysis or patient enrolment will generate the randomization schedule at the beginning of this trial. After providing informed consent, patients who are consistent with the inclusion and exclusion criteria will be randomly assigned to the treatment group or the control group. The randomization schedule will not be available to study recruiters or physicians. The allocation is only available for the independent data manager and the specific study coordinators in the Guancui EDC system. Specifically, when appropriate patients are enrolled, the researcher will inform the data manager, and then the random number and exact treatment group will be returned simultaneously.

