### Blinding

The patients, surgeons, anesthetists, data collectors, and outcome assessors are all blinded. Only the data manager and the specific study coordinator are unblinded to the group allocation. Unblinding by the investigator for a given patient will occur only if the knowledge of treatment assignment will materially change the planned management of a medical emergency. Investigators will have direct access to a given patient’s individual study treatment and the decision to unblind a patient’s treatment assignment in an emergency situation resides with the investigator; however, the investigator should attempt to contact the medical monitor or appropriate study personnel to discuss options before unblinding the patient’s treatment assignment unless the urgency of the medical situation precludes this.

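### The coordinator role that assesses and informs candidates is also the role given access to the allocation, so allocation concealment is not secured as written

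*Protocol article*

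**What the plan says.** Four statements in the protocol article bear on who knows the allocation.

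- **Who meets the candidates** (Participant enrollment and withdrawal): "Eligible patients will be assessed and informed by the specific study coordinators at the in-patient department".
- **Who holds the allocation** (Randomization): "The allocation is only available for the independent data manager and the specific study coordinators in the Guancui EDC system". The Blinding section repeats this in the singular: "Only the data manager and the specific study coordinator are unblinded to the group allocation".
- **Who must not have the list** (Randomization): "The randomization schedule will not be available to study recruiters or physicians".
- **How an assignment is released** (Randomization): "the researcher will inform the data manager, and then the random number and exact treatment group will be returned simultaneously". No recipient is named.

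The sequence is described in one sentence, "We applied a randomized block design with a block number of six in a 1:1 ratio", with no mention of varying block sizes or of stratification by centre. On timing, the section states "After enrollment, randomization and allocation will be done on the day of surgery". The data manager who generates the schedule is said to be independent of enrolment and of analysis. No such statement is made for the coordinators.

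**The concern.** Concealment requires that whoever decides whom to approach, and when to put a patient forward, cannot tell which arm comes next. Here the role that assesses and informs candidates carries the same distinctive name as the role that sees allocations. Read literally, staff who meet candidates know past assignments. With short fixed blocks, past assignments reveal some of the future ones.

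The stake is selection bias at entry. The primary outcome, the Comprehensive Complication Index within 30 days, can be expected to depend on a patient's baseline risk. If higher-risk candidates were approached or timed according to a predicted arm, the groups would differ before treatment. The planned comparison is a t-test or Mann-Whitney test without adjustment, which would not remove that difference.

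The release step adds a second gap. A treatment group, and not only a code, comes back after the researcher's request. If it comes back to that researcher, allocation knowledge reaches someone outside the two roles meant to hold it.

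**Working it through.** **1. Roles side by side.**

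| Function | Role named | Section |
|---|---|---|
| Assesses and informs candidates | specific study coordinators | Participant enrollment and withdrawal |
| Has the allocation in the EDC system | data manager; specific study coordinators | Randomization |
| Is unblinded | data manager; specific study coordinator | Blinding |
| Is denied the schedule | recruiters and physicians | Randomization |
| Is independent of enrolment | data manager only | Randomization |

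The coordinators appear in the first three rows and are not exempted in the last. If those who assess and inform candidates count as recruiters, they are denied the schedule but given the allocation.

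**2. Predictability when all earlier allocations are seen.** The plan states no figure here to reproduce. Inputs: block size 6 and ratio 1:1 (Randomization), read as a fixed 3:3 block. That gives C(6,3) = 20 equally likely sequences. An assignment is certain once one arm has used its three places. The best guess is always the arm with more places left.

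| Position in block | 1 | 2 | 3 | 4 | 5 | 6 | Sum |
|---|---|---|---|---|---|---|---|
| Certain beforehand | 0 | 0 | 0 | 0.10 | 0.40 | 1.00 | 1.5 |
| Guessed correctly | 0.50 | 0.60 | 0.60 | 0.70 | 0.70 | 1.00 | 4.1 |

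- Position 4 is certain when the first three are alike: 2/20 = 0.10.
- Position 5 is certain when the last two are alike: 8/20 = 0.40.
- Share certain: 1.5/6 = 25%.
- Share guessed correctly: 4.1/6 = 68.3%, against 50% by chance.

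The same figures hold at each site if blocks run within centre and the coordinator sees that site's allocations.

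**3. Predictability with one central list and an own-site view.** Inputs: seven centres (Study design). Equal recruitment is assumed, and the observer is generously assumed to know the position in the block. An assignment is then certain only if all three earlier patients in the exhausted arm came from the observer's own site, which has probability (1/7)³ = 1/343.

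- Share certain: 1.5 × (1/343) / 6 = 0.0007, or about 0.1%.
- Share guessed correctly, choosing the arm seen less often at the own site within the block: 53%, by enumerating all 20 sequences and all own-site patterns.

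**4. Would varying the block size be enough?** In a simulation with an illustrative mix of blocks of 4, 6 and 8 and unknown boundaries, an observer of all past allocations who always guesses the arm that is behind is still right about 68% of the time. Without sight of past allocations the figure is 50%. What matters is who can see the allocations.

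**The case against.** The strongest reply is that the text distinguishes the schedule, meaning the list of upcoming assignments, from the allocation of patients already randomized. Recruiters are denied the first, coordinators are given the second, and the Randomization section need not contradict itself. Assignment is also central, follows consent and enrolment, and draws on a list made by someone independent of enrolment. This is a fair reading, and for that reason it would be too strong to say that concealment fails outright. It does not settle the matter, because past allocations in short fixed blocks disclose part of what the schedule is meant to hide.

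A second reply is that this is one job title reused in a condensed article, and that duties and permissions may be separated in the full protocol. That may be so. The published wording still assigns both functions to one role and should then be corrected.

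Three stronger readings are tempting, and the document does not support them:

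- **That blinding fails.** The Blinding section states "The patients, surgeons, anesthetists, data collectors, and outcome assessors are all blinded" and openly declares the coordinator unblinded. Nothing says that coordinators collect data or judge outcomes.
- **That the enrolling researcher is told the arm.** The sentence on release names no recipient, and the one before it limits access to two roles. This is a gap in the text and does not show disclosure.
- **That about 45 remaining assignments were predictable.** This takes 25% of 300 − 120 = 180. The count of 120 dates from submission of the article, so the number outstanding later is unknown, and the 25% needs the visibility condition in step 2.

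**Conclusion.** The point holds as a conflict in the text that leaves allocation concealment unsecured. One named role both assesses and informs candidates and holds the allocation, and no statement separates the two functions.

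The size runs from about 0.1% known in advance and 53% guessable to 25% known and 68% guessable. The low end assumes one central unstratified list, seven equally recruiting sites and an own-site view. The high end assumes sight of the whole sequence, or blocks within centre. Both assume that the block number of six means a fixed block of that size. The protocol does not say which situation applies, so neither end can be taken as the estimate. Nothing in the document shows that any recruiter used allocation knowledge. The unnamed recipient of the treatment group is a smaller gap in the same procedure.

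**What to change.** - State, and enforce through EDC permissions, that anyone who screens, informs, consents or collects data has no access to allocations.
- Limit access to the data manager and one identified existing staff role that prepares the study drug, with no part in recruitment or data collection. The article names no preparer, so this role has to be specified.
- Return only a code to the enrolling researcher, and say who receives the treatment group.
- If the roles were already separate in practice, correct the enrollment, Randomization and Blinding sections to say so, and document the permissions that were in force.

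The cost is some reassignment of duties among existing staff, a permission change and a short amendment. Undisclosed varying block sizes are at most a secondary measure. Regenerating the schedule for that purpose is not needed, since step 4 shows that it gains little while the roles stay merged.
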